#### Randomization

A 1:1 blocked randomization scheme was utilized to yield “comparable” subjects in each of the 2 groups, stratified by birthweight (<750 g, 751–999 g, 1000–1250 g) within each site, to avoid imbalance in the distribution of the 2 groups at each site. We produced a separate block randomization list within each site for each subgroup (a total of three strata). The randomization is based on permutated blocks with random sizes varying from 2 to 4 (to avoid guessing) to make sure that each site will have an equal number of participants in each group. The randomization list was generated prior to study initiation using a random seed number via SAS PROC PLAN (SAS Inc., Cary, NC, USA) to generate the stratified randomization design. The statistician prepared sealed, numbered opaque envelopes for each site, with randomization assignment inside. The envelopes were given to the site’s research coordinator who assures that they are used in numerical order. After informed consent is obtained, the research coordinator opens an envelope, removes the group assignment form, writes the infant’s study ID # and date on the form, makes a copy of the form and sends it to the statistician, keeping the original in the infant’s study file. Group A (treatment) infants receive OMM, while Group B (control) infants receive a placebo (sterile water). In the case of a multiple birth, twins are stratified and randomized into either the intervention or the control group, and will be analyzed independently between the two experimental groups. Triplets or higher order multiple births are not be eligible for the study.

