##### Statistical analysis

Statistical analysis will be performed using an intention-to-treat (ITT) approach. Baseline infant and mother demographics and clinical characteristics will be summarized between milk and placebo groups using a chi-square or Fisher exact test for categorical variables (i.e. infant gender, race/ethnicity, socioeconomic status, maternal diagnosis of pre-eclampsia, premature and/or prolonged rupture of membranes, delivery mode, and steroid administration) and an independent *t* test or a Wilcoxon two-sample test for continuous variables (i.e. the time of initial exposure to mother’s own milk, duration [number of days] of central line placement and mechanical ventilation, gestational age, birth weight, post-natal steroids, antibiotic duration), depending on satisfying the normality assumption or not, respectively. A multivariable logistic regression with L-OS or NEC or death as the dependent variable, and group (milk versus placebo) as the primary independent variable will be constructed to assess the strength of association between oropharyngeal milk treatment and risk of L-OS or NEC or death, adjusting for pre-specified covariates including sex, gestational age and birth weight. Odds ratios and corresponding 95 % confidence intervals will be reported. Because the amount of mother’s milk that enrolled infants receive as a “feeding” will affect our study endpoints, we will closely monitor and record the total amount of mother’s milk received (percent of total feeding volume) for each study subject. We do not anticipate the amount of milk the infant receives as an enteral feed will be affected by group assignment. However, if we do observe a significant difference between the intervention and placebo groups, we will control for this variable in the regression models. While the main hypotheses will be tested using ITT analysis, we will also conduct per protocol analysis only for patients who complete the treatment. Completed treatment is defined as (the infant) having received 70 % of planned doses. However, this will be considered supplemental and exploratory, and the results will not be used as main conclusions of the study.

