##### Lactoferrin

We hypothesize that oropharyngeal administration of OMM will be associated with higher concentrations of urinary lactoferrin in treated infants. Our hypothesis is based on our pilot data [70], which showed higher concentrations of urinary lactoferrin in infants who received oropharyngeal administration of mother’s colostrum, compared to placebo-treated controls. No significant between-group differences were found; however, the sample size was small (*n* = 16). A large effect size (1.30) was noted for urinary lactoferrin, which suggests that results may have reached statistical significance if a larger sample had been used. This finding is consistent with research that has shown higher concentrations of urinary lactoferrin in mother’s milk-fed infants compared to formula-fed cohorts [90, 91]. Further studies have shown that the urinary lactoferrin is of maternal origin [92–94], although the precise mechanism of entry into the urine is unknown. The approach used to test this hypothesis will be the measurement of lactoferrin in urine samples at 3 time points (see Fig. 2), using a commercial ELISA assay. Lactoferrin concentrations will also be measured in milk samples from mothers, at the same three time points, to clarify whether the infant’s levels are due to the milk or from neonatal immune responses resulting from other factors. A mixed-effects regression model will be applied to assess whether the average at each time point or change over time is different between the two groups. The analysis will be done first for infant and mother separately, then an index variable will be created to define mother versus infant, and the difference between mothers and infants will be assessed. Appropriate variance-covariance structure will be determined by Akaike Information Criterion (AIC). Normality assumption will be evaluated using Shapiro-Wilk’s test or visualization of data distribution. Appropriate data transformation (i.e. log, square root) will be applied to correct the skewness.

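### Twins are to be analysed as independent infants with no term for within-pair correlation, so valid standard errors are not guaranteed; the direction of any error depends on a co-twin allocation rule that is not stated outright

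*Protocol article*

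**What the plan says.** The Randomization section of the protocol article describes a 1:1 blocked scheme, stratified by birth weight within site, using "permutated blocks with random sizes varying from 2 to 4". Each time an envelope is opened, the coordinator "writes the infant’s study ID # and date on the form". On multiple births it says that "twins are stratified and randomized into either the intervention or the control group, and will be analyzed independently between the two experimental groups", and that "Triplets or higher order multiple births are not be eligible for the study". The largest family in the trial is therefore two infants.

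The Statistical analysis section then names "A multivariable logistic regression with L-OS or NEC or death as the dependent variable", with treatment group as the main predictor and "adjusting for pre-specified covariates including sex, gestational age and birth weight". The section on safety endpoints adds chi-square and Fisher exact tests and Poisson regressions. None of these has a mother or family effect, a clustered variance or a paired analysis. The Sample size section makes no allowance for twins. The only mixed-effects model in the article is for lactoferrin, in the exploratory Aim 2.

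**The concern.** Co-twins share a mother, her milk, a gestational age and usually a NICU stay. The article itself ties late-onset sepsis (L-OS) and NEC to mother's milk and to NICU exposure, and it expects the amount of mother's milk fed to affect the endpoints. Correlated outcomes within a pair are therefore plausible. A model that assumes independence reports a standard error that is too small if co-twins sit in the same arm and too large if they are split. The 5 % level, the 95 % intervals and the 80 % power at 498 infants all assume independent infants.

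This is a written rule rather than a gap that an unseen analysis plan would fill. An analyst who follows the Randomization section as it stands would fit the models without any term for the pair.

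**Working it through.** **Inputs from the article (Sample size section).** L-OS 20 % versus 10 %, two-sided alpha 0.05, power 80 %, covariate R² = 0.2, 498 analysable (249 per arm), dropout 20 %, 622 enrolled.

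**Inputs assumed, because the article gives neither.** q = share of infants whose co-twin is also enrolled, 0.1 to 0.4. ρ = within-pair correlation of L-OS, 0.1 to 0.5.

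**Step 1: reproduce the plan's figure.** With mean risk 0.15,

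n per arm = [1.96·√(2·0.15·0.85) + 0.8416·√(0.2·0.8 + 0.1·0.9)]² / 0.1² = (0.990 + 0.421)² / 0.01 ≈ 199.

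Dividing by 1 − R² gives 199 / 0.8 = 248.75, so 249 per arm and 498 in total. Then 498 / 0.8 = 622.5, against 622 stated. Both figures reproduce, and both come from a formula for independent infants.

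**Step 2: design effect.** Let c be the probability that co-twins share an arm. There are qN/2 pairs. In the variance of the difference in proportions, a same-arm pair contributes a covariance of +2ρσ² and a split pair −2ρσ². So

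variance = (4/N²)·[Nσ² + (qN/2)·2ρσ²·(c − (1 − c))] = (4σ²/N)·[1 + qρ(2c − 1)].

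The ratio of true to assumed variance is D = 1 + qρ(2c − 1).

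**Step 3: value of c under three allocation rules.**
- Pair assigned together: c = 1.
- Each infant drawn independently, for example from separate birth-weight lists: c = 1/2.
- Consecutive envelopes from one list, blocks of 2 and 4 equally likely: a block of 2 has one within-block step (always split) and one step to the next block (split half the time), so 1.5 splits in 2 steps. A block of 4 has three within-block steps (each split with probability 2/3) and one step out, so 2.5 splits in 4 steps. On average that is 2 splits in 3 steps, so two thirds of pairs are split and c = 1/3. Simulating the list gave 0.668.

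**Step 4: consequences.** Type I error of the naive test = 2·[1 − Φ(1.96/√D)]. Power of an analysis with the correct variance uses 249·0.8/D infants per arm.

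| Allocation of co-twins | D | Type I error, naive test | Power at 498 |
|---|---|---|---|
| Same arm (c = 1) | 1.01 to 1.20 | 5.1 to 7.4 % | 79.7 to 72.5 % |
| Independent 50:50 (c = 1/2) | 1.00 | 5.0 % | 80.0 % |
| Two thirds split (c = 1/3) | 0.997 to 0.933 | 4.96 to 4.25 % | 80.2 to 82.7 % |

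Worst same-arm corner: q = 0.4 and ρ = 0.5 give D = 1.20, so 199.2/1.20 = 166 effective infants per arm and 72.5 % power. A middle case, q = 0.2 and ρ = 0.3, gives D = 1.06, type I error 5.7 % and power 77.7 %. Restoring 80 % power in the same-arm case would need 503 to 598 analysable infants (498·D), or 629 to 748 enrolled; the middle case needs 528 and 660.

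**Step 5: check by simulation.** Beta-binomial pairs, N = 498, common risk 0.15, unadjusted pooled z-test, 10,000 replicates, q of 0.2 and 0.4, ρ of 0.3 and 0.5. The ratio of true to naive standard error was 1.03–1.10 for same-arm pairs (type I error 5.6–7.0 %), 0.99–1.01 for independent allocation (4.5–5.1 %) and 0.96–0.99 with two thirds split (4.2–4.8 %). This agrees with the formula.

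**The case against.** The strongest reply is that the design described probably does little harm. The assignment form carries one infant's ID, and the strata are by birth weight, so co-twins can fall on different lists. Nothing says that a pair shares an arm. With infant-level allocation, same-arm and split pairs nearly cancel, or splits predominate and the naive test errs on the safe side. This stands. A reader might infer from the twin rule that the standard errors are definitely wrong, or that type I error is inflated and the trial underpowered. The article does not support that: those results need co-twins to share an arm, which it never says.

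The model also adjusts for gestational age, which twins share, and for birth weight. That should remove part of the crude correlation, so ρ is best read as what remains after adjustment, and the upper end of the range is generous.

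It can also be said that the twin sentence means only that each infant is counted in the arm it drew. That reading is possible, but the models still contain no pair term, and the sentence would still send an analyst to an independence analysis.

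On lactoferrin, the article says that "Lactoferrin concentrations will also be measured in milk samples from mothers, at the same three time points", without mentioning twins. It does not say that a twin mother's sample is entered twice, so double counting is an inference. The aim is exploratory and a mixed model is already planned there. It remains a secondary point.

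**Conclusion.** The point holds in limited form. The article commits to treating twins as independent, and none of the named clinical or safety models allows for correlation within a pair, so valid standard errors are not assured. Which row of the table applies turns on a rule the article leaves unstated. The effect is about nil under individual allocation, which the text favours, and mildly conservative with a small loss of precision if short blocks split most pairs. Only if pairs are assigned together does it become a moderate problem for the 5 % level and the power. All sizes rest on the assumed twin share and correlation; the actual values could fall anywhere in those ranges or outside them. The case for changing the text is that a clustered analysis is valid under every allocation rule, not that the present one is known to fail.

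**What to change.** 1. In the Randomization section, replace the commitment to independent analysis with one prespecified method: logistic GEE clustered on mother, exchangeable working correlation and robust standard errors, for L-OS, NEC and death, and the matching Poisson GEE for safety counts. Name this method alone. A mother random intercept targets a mother-specific odds ratio rather than the population-average one, and it is weakly identified when most families contribute one infant. With 498 infants there would be roughly 398 to 473 mothers (498·(1 − q/2)), enough for robust standard errors.
2. State whether co-twins are randomised singly or as a pair.
3. If they are randomised as a pair, restate the power at 498 with the design effect 1 + twin share × within-pair correlation, giving the values assumed for both.
4. As a secondary point, in the exploratory lactoferrin model let each mother's milk sample enter once.

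**Cost.** Slightly more analysis work, and no extra infants for the change of method. The dataset must hold an infant-to-mother link. The article does not say that a mother identifier is recorded, but giving each infant its own mother's milk implies that the link exists in practice. The article reports 77 enrolled, 11 of them screen failures, against a target of 622, so the change can still be made early.

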##### Retention

The major issue with retention is the need for mothers to provide milk until their infant reaches 32 weeks CGA. While most will be motivated to do so (based on our experience) we have conservatively estimated a 20 % dropout rate to account for mothers who discontinue pumping (based on previous experience). Only a very small volume (< ½ teaspoon) of milk is needed daily for the intervention and, as our pilot data shows that all mothers can readily express this amount, this should not be problematic.

#### Study procedures

##### Collection of milk

Research personnel within each site have been trained, using a standardized protocol (Protocol version 4; Dated 1/5/2015), to assure coherence of data collection. Mother’s milk samples are collected during the routine expression of milk, using a hospital-grade electric breast pump, and are stored in the NICU breastmilk refrigerator. When at least 2.5 mL (½ teaspoon) of mother’s milk is available, the research nurse prepares the syringes for the first 24 hours of the Initial Treatment Period. For infants in the placebo group, the milk is immediately frozen, in a separate NICU breastmilk freezer to maintain blinding, for later use when enteral feedings are started. Using sterile gloves, 24 sterile oral syringes are each filled with 0.1 mL of OMM or sterile water (based on group assignment), capped, and covered with a white tape as a blinding procedure. Each syringe is labeled with the patient’s name, medical record number, and the date and time of preparation. Syringes are prepared in the same sterile manner, by the research nurse, every 24 hours. For the Extended Treatment Period, a total of 16 syringes are prepared daily, for treatments to be given every 3 hours.

It is standard practice to encourage mothers of extremely premature infants to pump frequently (typically every 3 hours) in order to establish and maintain an abundant milk supply. Therefore, it is common for NICU nurses to see several containers, with varying amounts of mother’s milk, in the NICU refrigerator, on a daily basis. The milk is either used for enteral feeds or frozen for storage. Since only miniscule volumes of milk are needed daily for this intervention (2.4 mL and 1.6 mL per day, for Initial and Extended Treatment Periods, respectively) it has been our experience that NICU nurses do not notice that a small volume of milk has been removed from the refrigerator, and thus they remain blind to group assignment.

##### Oropharyngeal administration procedure

Using a standardized protocol, the nurse provides the dosing as follows: two syringes are warmed to room temperature. The first syringe’s cap is removed and the tip of the syringe is gently placed into the infant’s mouth, alongside the right buccal mucosal tissue. The syringe tip is directed posteriorly towards the oropharynx, and the total volume (0.1 mL) is slowly administered, over at least 1 minute. The second syringe is placed in the infant’s mouth in the same manner, but alongside the left buccal mucosal tissue. The entire volume (0.1 mL) is administered slowly, over at least 1 minute. A petite swab is used to carefully swab the right buccal mucosal tissue, followed by the left buccal mucosal tissue (≤5 seconds each side). A total volume of 0.2 mL is administered per treatment, with buccal swabbing taking place over 10 seconds. Vital signs are carefully monitored throughout the procedure. The procedure is repeated every 2 hours for 48 consecutive hours during the Initial Treatment Period, which begins within the infant’s first 96 hours of life. The Extended Treatment Period begins immediately after the Initial Treatment Period has been completed and ends when the infant reaches 32 weeks CGA as depicted in Fig. 2. Dosing is provided every 3 hours during the Extended Treatment Period. Participation in this study does not interfere with the initiation or progression of enteral feedings, which is left to the discretion of the attending physician. Urine, oral mucosal swabs, and stool specimens are collected from enrolled infants, and milk samples from their mothers, at specific time points, as depicted in Fig. 2.

**Fig. 2 Fig2:**
[figure not shown]
Study flow chart. Enrolled infants are randomized to receive either own mother’s milk or a placebo during the initial treatment period and the extended treatment period. Biological specimens (milk, urine, stool and swab of oral mucosa) are collected at specific time-points as depicted. CGA, corrected gestational age; L-OS, late-onset sepsis; NEC, necrotizing enterocolitis

##### Objectives

Our specific Aim 1 is to compare the effects of oropharyngeal administration of mother’s milk to a placebo, for important clinical outcomes, including (1A) reducing the incidence of L-OS (primary outcome) and (1B) NEC and death. Our specific Aim 2 is to identify the biomechanisms responsible for the beneficial effects of oropharyngeal administration of mother’s own milk for extremely premature infants including (2A) enhancement of gastrointestinal (fecal) microbiota (2B) improvement in antioxidant defense maturation or reduction of pro-oxidant status, and (2C) maturation of immunostimulatory effects as measured by changes in urinary lactoferrin.

##### Sample size/Power analysis

We hypothesize that extremely premature infants who receive oropharyngeal administration of mother’s milk will have a significantly lower incidence of L-OS (primary endpoint). Based on recent (2012) data from the Vermont-Oxford Network that included > 20,000 ELBW infants, the incidence of L-OS in this population was 19.4 %. Based on data from Manzoni et al. [14], that showed a reduction of L-OS from 17 % to 6 % with exogenous bovine lactoferrin in preterm infants, we conservatively estimate a reduction in L-OS from 20 % to a total of 10 % in milk-treated infants. Since Manzoni et al. [14] used a lactoferrin dose similar to that in mother’s milk, and based on studies that mother’s milk reduces L-OS [6–8] this effect size of reduction (from 20 % to 10 %) should be realistic and obtainable given the patient population. Since many variables may alter the risk for L-OS in extremely premature infants multivariable logistic regression (for dichotomous L-OS outcome) will be performed adjusting for covariates such as sex, gestational age and birth weight. Power calculations were determined using PASS 14.0 software (NCSS, LLC, Kaysville, UT, USA). We estimate that up to a total of 10 covariates will account for a combined 20 % (*R*^*2*^ = 0.2) of variance in the regression model. Based on a 2-tailed alpha of 0.05 and 80 % power, a sample size of 498 (249 in each group) will be needed to reach a statistical power of 80 % to detect a difference of 10 % versus 20 % (effect size odds ratio (OR) = 0.44) in L-OS outcome between milk and placebo groups. Therefore, the study is adequately powered for the primary endpoint L-OS. The study sample is being accrued from 5 sites and, based on a lactation initiation rate of > 70 % for all sites (conservative, based on actual rates of 80–90 %), and an estimated refusal rate of 30 % (a conservative estimate based on our previous experience in recruiting subjects for this intervention), we will screen a total of 1270 patients to enroll 622, with an estimated dropout rate of 20 %, that will allow us a complete analysis for 498 subjects.

##### Outcome measures for specific Aim 1

Primary endpoints: L-OS is defined as the new onset of at least 2 clinical symptoms with a positive blood culture (noted after Day of life 3) and identification of an organism known to be a cause of sepsis rather than a contaminant. If the blood culture shows a potential contaminant (such as *Staphylococcus epidermidis*) a second blood culture is obtained to confirm the presence of bacteremia.

Secondary endpoints: NEC and death. NEC is defined according to modified Bell’s criteria stage > 2 with clinical signs and radiological evidence including any of the following: pneumatosis intestinalis, portal venous gas with or without pneumoperitoneum.

Covariates: sex, gestational age and birth weight will be included as covariates.

Safety endpoints: health outcome and safety data are closely monitored and collected throughout the infant’s stay until discharge or death. Infant safety is being assessed through the monitoring for adverse events by the Data Safety and Monitoring Board (DSMB), comprised of independent reviewers. The DSMB meets every 6 months during the first year of active enrollment, and thereafter at ¼, ½ and ¾ enrollment to ensure rapid identification of adverse events. Adverse events are defined to include aspiration, significant bradycardia following (oropharyngeal milk) administration leading to the need for resuscitation, and post-natal acquisition of cytomegalovirus (CMV) thought to be associated with fresh milk. Studies have identified the potential risk of milk-acquired CMV infection, but based on the small volumes and controversial risk (even with frozen milk), we promote fresh milk as our standard in this study, as we did with our pilot studies, and follow clinically for symptoms of acquired CMV and will intervene quickly if a case should arise. To maintain safety of enrolled infants, vital signs are carefully monitored during the oropharyngeal administration of the study substance (milk or sterile water). The nurses are instructed to immediately stop the procedure and to notify the site PI if any of the following signs of aspiration should occur: an increase in fraction of inspiratory oxygen > 0.1 to maintain a SpO_2_ > 85 %, bradycardia (heart rate (HR) < 100/minute), tachycardia (HR > 200/minute), tachypnea (respiratory rate (RR) > 80/minute), or apnea. Treatments are withheld during surgical and invasive procedures or based on clinical evidence of acidosis, NEC, multisystem organ failure, or other instances of clinical deterioration, but this decision is left to the discretion of the attending physician after discussion with the site PI (another neonatologist).

Built into this study, are interim analyses by the DSMB that will evaluate any significant adverse events that may require altering study protocol over the course of the study, and to analyze whether results with one arm are not significantly beneficial compared to the other. Adverse events could occur in the intervention and placebo groups (for bradycardia and aspiration). Ad-hoc DSMB meetings can be requested at any time if the PI or site investigators identify a potential safety issue. The PI is responsible for accurate documentation, investigation and follow-up of all study-related unanticipated serious events in a timely manner. To ensure that study-related unanticipated serious events are identified and managed expeditiously, the following reporting mechanism will be implemented: the PI ([name]) will be notified immediately by the site investigator (collaborating neonatologist) of any study-related unanticipated and adverse events or serious safety issues. The PI will immediately request an ad-hoc DSMB meeting to review safety data. The DSMB will review the study-related unanticipated and adverse events and will make a determination as to whether the study should be continued, modified or terminated. The DSMB Chair will forward the report to the PI, who will submit the report to the NorthShore IRB and to site investigators (collaborating neonatologists) at each study site, who must, in turn, submit the report to their local IRBs. The report will include the DSMB’s recommendations to the IRB as to whether the study should be continued, modified or terminated. Any action taken by the IRB will be reported by the PI to the DSMB, and to site investigators and their IRBs.

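### The 498 rests on a misapplied R² = 0.2 inflation: on the stated rates 498 analysed infants give about 87–88 % power, not 80 %, so the error is conservative

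*Protocol article*

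**What the plan says.** All the inputs stand in the Protocol article, section Sample size/Power analysis. The error rate and target are given as "Based on a 2-tailed alpha of 0.05 and 80 % power". The effect is given as "to detect a difference of 10 % versus 20 % (effect size odds ratio (OR) = 0.44"). The covariate allowance reads "We estimate that up to a total of 10 covariates will account for a combined" 20 % (R² = 0.2) of the variance of the regression model, and it follows a remark that many variables may affect the infant's risk of late-onset sepsis. The result is "a sample size of 498 (249 in each group) will be needed". The same section names PASS 14.0 as the software but not the procedure or formula. It then allows 20 % dropout and arrives at 622 enrolled.

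Two other sections bear on the covariate allowance. Randomization says "A 1:1 blocked randomization scheme was utilized", in permuted blocks, stratified by birth weight within each site. Statistical analysis describes the logistic model as "adjusting for pre-specified covariates including sex, gestational age and birth weight". All three named covariates are fixed before allocation. That section adds one conditional covariate, the share of feeds given as mother's milk, to be included only if it differs significantly between the groups.

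**The concern.** The paragraph treats R² as a measure of how well the covariates explain the outcome model. In the usual sample-size formula for a logistic regression coefficient, the factor 1/(1 − R²) corrects for something else: overlap between the covariate of interest, here treatment, and the other covariates. Overlap matters in an observational study, where exposure and confounders go together. Randomisation is designed to remove it. Covariates that predict the outcome but are unrelated to treatment do not call for this inflation.

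If the wrong quantity was entered, the stated link between 498 infants and 80 % power for the primary endpoint is incorrect. A steering group or data monitoring board that relies on the paragraph, for example when recruitment is slow or a sample-size change is discussed, would then misjudge how much room the trial has.

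**Working it through.** **Inputs** (Protocol article, Sample size/Power analysis): placebo rate P₀ = 0.20, milk rate P₁ = 0.10, two-sided alpha 0.05 (z = 1.960), power 0.80 (z = 0.8416), R² = 0.2, dropout 20 %. Allocation is 1:1 (Randomization), so B = 0.5 and the mean rate is 0.15.

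**Check of the effect size.** OR = (0.1/0.9)/(0.2/0.8) = 0.444, which agrees with the stated 0.44.

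**Reproducing 498.** The logistic formula for a binary covariate, equal at 1:1 to the pooled two-proportion formula, is

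N = [z(α/2)·√(P̄(1−P̄)/B) + z(power)·√(P₀(1−P₀) + P₁(1−P₁)(1−B)/B)]² / [(P₀−P₁)²(1−B)], then divided by (1 − R²).

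- First term: 1.960 × √(0.1275/0.5) = 1.960 × 0.5050 = 0.9897.
- Second term: 0.8416 × √(0.16 + 0.09) = 0.8416 × 0.5 = 0.4208.
- N = (1.4105)²/(0.01 × 0.5) = 397.9, that is 398 (199 per arm).
- With R² = 0.2: 397.9/0.8 = 497.4, that is 498 in two equal arms of 249. **This is the stated figure.**
- Dropout: 498/0.8 = 622.5, against 622 enrolled.

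Other formulas do not give 498. Before and after division by 0.8, the continuity-corrected version gives 438 and 548, and the Wald log-odds-ratio version gives 414 and 518. The unpooled version gives 392 before inflation.

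**What R² should be here.** In this formula R² comes from regressing the treatment indicator on the other covariates. With ten baseline covariates and 498 randomised infants its expected value is about 10/497 = 0.02. A simulation of simple 1:1 allocation gave a mean of 0.020 and a 99.9th percentile of 0.054. A value of 0.2 is far outside that range.

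**Results with other values of R².** Power at 498 is Φ{[√(498(1−R²) × 0.005) − 0.9897]/0.5}.

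| R² (treatment on covariates) | N for 80 % power | Power at 498 |
|---|---|---|
| 0 | 398 | 88.0 % |
| 0.02 | 406 | 87.4 % |
| 0.05 | 419 | 86.4 % |
| 0.2 (as planned) | 498 | 80.0 % |

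**Taking the wording at face value.** Suppose R² = 0.2 does mean outcome variance explained, on the latent logistic scale (an assumption), with marginal rates of 20 % and 10 %. Simulated power of the adjusted test at 498 is then about 91 %, and of the unadjusted test about 88 %. This reading does not give 80 % either.

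**The case against.** **The sum is right.** Given R² = 0.2, 498 follows exactly, and 622 follows from 498. This stands: the fault lies in the choice and description of one input, not in the arithmetic. The formula is also inferred from an exact match, since the document names only the software.

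**The error does no harm.** A reader told that the sample size is wrong might infer that the trial is too small. The documents do not support that. The figure exceeds what 80 % power requires by 92 to 100 infants (498 − 406, 498 − 398), and the protocol's statement that the study is adequately powered remains true on its own rates.

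**The 0.44 might be meant as a covariate-adjusted odds ratio.** The planned analysis does report an adjusted one. If the adjusted odds ratio is 0.44 and the covariates explain 20 % on the latent scale (both assumptions), the marginal rate in treated infants is about 10.7 %. Simulated power is then about 77–78 % at 398, close to 80 % at 420 and about 85 % at 498. This narrows the excess without removing it. The reading is also the less natural one, because 0.44 is exactly the odds ratio implied by 20 % and 10 %.

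**One covariate may not be a baseline variable.** The mother's-milk share of feeds would enter the model only when it is related to treatment, so the chance bound would not then apply. But the protocol says "We do not anticipate the amount of milk the infant receives as an enteral feed will be affected by group assignment", so this cannot be the basis for 0.2.

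**The 87–88 % is not the trial's certain power.** It takes the planning rates as true and treats infants as independent, although twins are enrolled and analysed independently. This stands as a condition on the figure.

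**The excess might be read as needed cover for dilution under intention-to-treat.** The plan makes no such claim. A calculation with, say, 20 % against 12 % assumes that every infant in the 20 % dropout gains nothing. Retention ties dropout to mothers who stop pumping, whose infants may already have had many doses, and Discussion reports more than 90 % of planned treatments given so far.

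**Conclusion.** The concern holds as a misapplied and misdescribed input. The inflation by 1/(1 − 0.2) belongs to correlation between treatment and covariates, which 1:1 stratified randomisation with baseline covariates leaves at about 0.02. The claim that 498 infants are needed for 80 % power is therefore incorrect as written. For 20 % against 10 %, two-sided 0.05, independent infants and a treatment–covariate R² of 0 to 0.02, 498 gives 87.4–88.0 % power, and 80 % needs 398 to 406. The misstatement is 7 to 8 percentage points of power, in the conservative direction. It does not show a shortfall, an arithmetic slip, or a need to change enrolment.

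**What to change.** Rewrite the power paragraph in Sample size/Power analysis:

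- Remove the R² = 0.2 inflation, or set R² to 0–0.02 and define it as the share of the treatment indicator's variance explained by the other covariates.
- Keep 498 analysed and 622 enrolled.
- State that 498 gives about 87–88 % power for 20 % against 10 %, or say explicitly that the number above 398–406 is a deliberate margin.
- Name the formula or software procedure, and say whether 0.44 is the marginal or the adjusted odds ratio.
- If dilution under intention-to-treat is offered as a reason for the margin, show it as a separate calculation with its assumption labelled.

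The cost is one paragraph of text. Enrolment, endpoint, alpha and analysis model do not change.
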